### Secondary Outcomes

We will also assess anthropometrics, body composition, blood pressure, resting pulse, demographic information, health status and quality of life, physical function, exercise motivation, self-regulation, and psychological feelings toward exercise.

Anthropometrics include height (cm), weight (kg), and BMI (*kg*/m^2^). To ensure accurate measurement of anthropometrics, height and weight will be measured to the nearest 0.1 unit. Participants will be instructed to remove their shoes and any bulky clothing before measurement. Height will be measured using a portable stadiometer [63] and weight will be measured using a calibrated electronic scale [64]. The same equipment will be used at both clinics. The electronic scale will be transported in a cushioned carrying case to ensure it remains calibrated. BMI will be calculated by converting height into meters and squaring that value, then dividing weight by this value [65].

Body composition will be estimated based on the waist circumference (cm), hip circumference (cm), and waist-to-hip ratio. The waist will be measured at the smallest circumference of the torso, while the hip will be measured at the largest circumference at or below the anterior superior iliac spine [66]. The waist-to-hip ratio will be calculated by dividing the waist circumference by the hip circumference [66]. The average from three measurements of anthropometrics and body composition will be used.

Blood pressure and resting pulse will be measured by a sphygmomanometer (Omron BP742N, Lake Forest, IL) [67]. Blood pressure will be measured after the participant is seated for at least five minutes and before any other measurements are taken. The sphygmomanometer is validated for clinical and personal use according to the European Society of Hypertension International Protocol [67].

Demographic information will be collected at both assessments. This information includes date of birth (age), race/ethnicity, educational level, comorbid conditions, and medication use. The 36-Item Short Form Health Survey will be used to estimate health status and quality of life. Subscales of this instrument include physical functioning, social functioning, physical role limitations, emotional role limitations, mental health, energy/vitality, and pain [68].

Physical function will be measured objectively and subjectively. Physical function will be objectively assessed using the short physical performance battery. Total functional capacity is based on a composite score from the following subtests: repeated chair stands, balance (semitandem stand, side-by-side stand, tandem stand), and 8 feet up walk [69]. Physical function will be subjectively assessed using the PROMIS Short Form v1.2-Physical function 8b [70].

Several self-report measures will be used to estimate exercise motivation, self-regulation of exercise, and psychological feelings toward exercise [55,71,72]. Each measure includes subscales. Exercise motivation consists of intrinsic motivation, identified, introjected, external regulation, and amotivation [71]. Self-regulation consists of exercise goals and exercise plans [55]. Psychological feelings toward exercise consist of perceived competence, perceived autonomy, and perceived relatedness [72].

### Focus Groups

We will conduct several focus groups with research participants at the end of the intervention to further evaluate feasibility and acceptability. These sessions will consist of 5-8 individuals and last for 1.5-2 hours. A trained professional will facilitate all of the focus groups. Groups will be separated based on the intervention modality and two groups will be completed for each study arm. The focus groups will explore the perceived effectiveness of the 5 A’s counseling and the monitoring device. Participants will also be asked questions pertaining to their overall feelings toward the intervention and their thoughts of the intervention being implemented through their primary care physician.

Focus groups following the same structure, but with primary care stakeholders, will also be conducted at the conclusion of the intervention. Stakeholders (n=20) will consist of medical doctors, nurses, medical residents, physician assistants, and other staff personnel. Stakeholders will be recruited through coordination with the Department of Internal Medicine and Family Medicine at the clinics used in the study. All stakeholders will consent to be a part of the focus group and will be given the opportunity to wear the UP24 for one month. During the focus groups, stakeholders will be asked questions related to their perception of the intervention. Materials and equipment from the intervention will be provided and preliminary results of the intervention will be presented. The goal of the focus groups is to elicit reactions regarding the feasibility and acceptability of including this intervention into their primary care clinic. Stakeholders will also be asked about their familiarity with 5 A’s counseling and the extent of its use in practice. Stakeholders will complete a brief questionnaire before and after the focus group. In addition, stakeholders that wear the UP24 for one month will complete a feasibility questionnaire upon returning the monitor.

### Statistical Analyses

The Statistical Package for the Social Sciences (version 20) will be used to perform all quantitative statistical analyses. Analyses will be completed in two ways: first using the intent-to-treat principle (primary analysis) and then only with adherers to the intervention (secondary analysis for the purpose of informing further intervention refinement). The alpha-level to determine significance is set at .05. The specific statistical procedures, by research aim, are described below.

### Aim 1

Feasibility findings will be primarily descriptive and used as a metric for improvement when compared to similar studies. For example, days worn will be compared to other EAM studies, whereas attrition will be compared to other primary care-based studies. Rather than determine dichotomous feasibility or not, we will use relative feasibility to determine areas of focus for intervention refinement; which is addressed in the follow-up questionnaire and in focus groups. Comparisons of adherence between EAM and pedometer groups is covered under Aim 2 below and the procedures for analyzing focus groups will be identical to procedures outlined in Aim 3 below.

We hypothesize that the intervention will be feasible among several improvement metrics including ≥ 70% days the monitor is worn [37], < 20% attrition [73], and < 8 moderate or higher adverse events (< 20% of participants reporting an adverse event) [74-76]. Hypotheses based on other feasibility metrics include a low frequency of technical difficulties and a high frequency of app usage. Additionally, the intervention will be accepted among participants based on self-report questionnaires and focus group responses. We also hypothesize that the EAM group will show higher feasibility and acceptability compared to the pedometer group.

### Aim 2

Descriptive analyses will be conducted using means and frequencies for baseline characteristics. These characteristics include age, gender, race/ethnicity, educational level, CVD risk, PA, fitness, weight, BMI, blood pressure, pulse, wait and hip circumference, physical function, exercise motivation, health status, psychological feelings, and self-regulation. Mean group differences will be examined using independent samples *t* tests for normally distributed data and nonparametric tests (Kruskal-Wallis and Mann-Whitney U) for nonnormally distributed data. Differences in variable frequencies will be examined using chi-square tests. Little’s Missing Completely at Random test will be performed to determine whether outcome data are missing at random.

Analysis of covariance will be used to test the postintervention difference at 12 weeks (PA, CVD risk, fitness) between the two groups. The covariates in the analysis will include baseline values of the dependent variable, clinic location, and any variables significantly different between groups at baseline. A blinded statistician will conduct analysis on the primary outcome variables (PA, CVD risk, fitness). This same procedure will be used to assess differences in weight, BMI, body composition, health status, motivation, physical function, psychological feelings, and self-regulation. Group mean values for adherence variables at 12 weeks (retention rate, days the monitor worn) will be analyzed by an independent *t* test.

The primary purpose of this study is to evaluate its feasibility and acceptability; therefore, the analyses described in this section are exploratory and no prespecified power calculation is needed. Although this is a pilot study and it is not powered to detect significant difference in small-to-moderate effects, we hypothesize that the EAM group will demonstrate greater improvement in all of the aforementioned variables compared to the pedometer group.

### Aim 3

NVivo 11 Pro (QSR International) will be used to perform qualitative analyses. Thematic analysis will be conducted to analyze the focus groups [77]. Codes will be developed prior to the focus groups. Additional coding will be processed while the focus groups are conducted, adding codes based on new data. After including all study participants, the completed code list will be used to code transcripts of all groups. The PRECIS tool will also be used to estimate the intervention’s potential success in real clinical app [78].

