#### Grouping the Participants

All participants will be given an activity monitor to encourage self-regulation of PA. After counseling, participants will be randomized to one of the two groups: pedometer or EAM group. A random number generator available on the Internet will be used to randomly allocate group assignment [50]. Assignment into the EAM group will be selected randomly by the generator using the following settings: 1 set, 5 unique numbers, numbers range from 1 to 10, and sorted lowest to highest. This process will be repeated for 3 more sets of numbers ranging from 11-20, 21-30, and 31-40. Each number represents a participant identification number selected to be in the EAM group. Group assignment will be written on a piece of paper wrapped in foil and carbon paper and concealed inside an envelope prior to group allocation. A blinded researcher will prepare all of the envelopes. After group allocation, participants will be given all intervention materials and detailed instructions on all intervention components. For participants in the EAM group, the researcher will also test the monitor and the participant’s smart device to ensure they are working properly. Due to the nature of the intervention, the participants and the accessor will not be blinded to group assignment after randomization.

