### Power Calculation

Although the aim of the intervention is to improve behavioral and health outcomes related to cardiovascular risk, the primary purpose of this study is to investigate the feasibility of intervention components and study procedures and to inform a larger intervention. This is necessary in research related to CVD [79]. For these reasons, a sample size of 40 was deemed appropriate to test the intervention. The sample size of 40 is able to detect an increase of 1000 steps from baseline to follow-up, which is below the minimum expected increase in steps from pedometer-based interventions [80]. The findings from this pilot study will be used to establish initial effect sizes and inform the power and sample size estimates for future larger trials.

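### The Aim 2 ANCOVA adds covariates because they differ significantly at baseline, so part of the adjustment set is chosen by chance imbalance rather than by prognostic value

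*Protocol article*

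**What the plan says.** The rule is in the Protocol article, Statistical Analyses, Aim 2: "The covariates in the analysis will include baseline values of the dependent variable, clinic location, and any variables significantly different between groups at baseline". The clause at issue is the last one, "any variables significantly different between groups at baseline". The rule governs the 12-week comparisons of physical activity, cardiovascular risk and fitness, and the same section extends the procedure to the secondary outcomes.

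The variables that feed the rule are in the paragraph before it. That paragraph opens descriptively ("Descriptive analyses will be conducted using means and frequencies for baseline characteristics"), lists the characteristics ("age, gender, race/ethnicity, educational level, CVD risk, PA, fitness, weight, BMI, blood pressure, pulse, wait and hip circumference, physical function, exercise motivation, health status", followed by psychological feelings and self-regulation), and then moves to tests: t tests, nonparametric tests and, for categorical variables, "Differences in variable frequencies will be examined using chi-square tests". The threshold is the general one: "The alpha-level to determine significance is set at .05". No separate level for baseline tests, cap on the number of covariates or prognostic criterion is given anywhere in the article.

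Allocation is randomised 1:1 in blocks of ten (Grouping the Participants: "1 set, 5 unique numbers, numbers range from 1 to 10, and sorted lowest to highest", repeated for three more sets), giving 20 per arm. Aim 2 is called exploratory. The Power Calculation section says the findings will supply initial effect sizes and inform sample sizes for later trials.

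**The concern.** If allocation was random and concealed, any significant baseline difference between arms is a chance event. A test of that difference cannot show which variables need adjustment. What matters for an adjusted comparison is how strongly a covariate predicts the outcome, and the p-value for imbalance says nothing about that. Under this rule a strongly prognostic variable with p = .10 is left out, while an unrelated one with p = .04 goes in.

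Two things are at stake. The first is precision: a covariate that is imbalanced between arms but unrelated to the outcome overlaps with the treatment indicator and removes no residual variance, so the standard error rises. The second is interpretability: the meaning of the adjusted difference depends partly on which baseline tests happened to cross .05, which makes it harder to carry into the planning of a larger trial.

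**Working it through.** The protocol gives no figure for the number of baseline tests or expected imbalances, so there is none to reproduce. Its one sample-size statement (1000 steps with 40 participants) has no standard deviation or power, and nothing below depends on it.

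**Inputs.** N = 40 (Power Calculation: "a sample size of 40 was deemed appropriate to test the intervention"); 20 per arm (Grouping the Participants); alpha .05, taken as two-sided because sidedness is not stated.

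**Number of variables tested.** This is our count; the protocol does not say whether each subscale is tested.
- Headings listed under Aim 2: 17.
- Expanded with the measures and subscales in Table 4 and the Secondary Outcomes section: age, gender, race/ethnicity, education (4) + Framingham risk (1) + six minute walk (1) + physical activity (2) + weight, BMI (2) + systolic and diastolic pressure (2) + pulse (1) + waist, hip (2) + physical function (2) + motivation (5) + SF-36 (7) + psychological feelings (3) + self-regulation (2) = 34. Adding waist-to-hip ratio gives 35.

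**Expected chance selections**, k × .05:
- 17 × .05 = 0.85
- 34 × .05 = 1.70
- 35 × .05 = 1.75

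**Probability of at least one**, 1 − .95^k, if independent:
- k = 17: 58.2%
- k = 34: 82.5%
- k = 35: 83.4%

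For k = 34, the probability of at least two is 51.2% and of at least three 24.1%.

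**Correlated variables** (simulation, 20 per arm, 6000 runs per setting; the correlations are assumptions). With 34 variables the expected number stays near 1.7, but the probability of at least one falls:
- within-domain correlation 0.5 to 0.7: about 74% to 78%
- common correlation 0.3: 70%
- common correlation 0.5: 54%

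Selections then cluster, with five or more in about 5% to 10% of runs. With 17 variables at a common correlation of 0.3, the probability is 51%.

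**Cost of one selected covariate unrelated to the outcome.**
- Critical t on 38 df = 2.024, so a continuous variable is selected only if the arms differ by at least 2.024 × √(1/20 + 1/20) = 0.64 SD.
- Squared correlation with arm: r² = 2.024² / (2.024² + 38) = 0.097.
- Variance inflation: 1 / (1 − 0.097) = 1.108, about 11%.
- Standard error inflation: √1.108 = 1.053, about 5%, plus one degree of freedom.

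This is a minimum, because a larger imbalance gives a larger r².

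**Whole rule against the two fixed covariates** (simulation, 34 variables; all effect and correlation inputs assumed).

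| Setting | Fixed covariates only | With the rule |
|---|---|---|
| Mean SE, added covariates not prognostic, within-domain correlation 0.5 | 0.223 | 0.249 |
| Power for an assumed 0.6-unit effect, same setting | 74% | 65% |
| Type I error, same setting | 0.047 | 0.046 |
| Type I error, some tested covariates prognostic | 0.054 | 0.040 |
| Mean SE, some tested covariates prognostic | 0.292 | 0.324 |

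The SE ratio in the first row is 0.249 / 0.223 = 1.12.

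**The case against.** The strongest defence is that little depends on this model. Aim 2 is labelled exploratory and feasibility is the stated primary purpose. Wear days, attrition and adverse events do not pass through the ANCOVA, and adherence is compared by t test. This stands, and it limits the severity.

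Several stronger readings are tempting, and the documents do not support them.

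- **That the analysis is not prespecified.** Two covariates are fixed for every outcome, including the outcome's own baseline, usually the most useful one. The rest follow a stated rule that uses baseline data only, and a blinded statistician analyses the primary variables. Only the identity of the added covariates is left open.
- **That the rule produces false positives.** The simulations show no type I inflation; where some tested covariates were prognostic the test became conservative.
- **That collinearity damages the estimate**, for example blood pressure in the model for the Framingham score. A covariate correlated with the outcome is a prognostic one and generally helps precision. Correlation among adjustment covariates does not in itself harm the treatment estimate.
- **That a chance covariate is certain to enter, or that 83% is the figure.** That value needs about 34 tests and independence, which is implausible for weight, BMI and waist, or for subscales of one questionnaire.

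It is also fair to say that many listed variables (age, BMI, fitness, activity) may be prognostic, and adjusting for them would recover some of the lost precision. The 12% rise in standard error assumes that none of the added covariates is. None of this turns imbalance testing into a sound way of choosing covariates.

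**Conclusion.** The point holds as a moderate one. The clause selects covariates on chance imbalance, and nothing else in the article limits it. Expect 0.85 to about 1.7 such selections. The probability of at least one is 58% to 83% under independence across 17 to 35 tests, and roughly 54% to 78% for 34 tests under the correlations assumed. Each continuous covariate selected without being related to the outcome costs at least about 11% in variance, about 5% in standard error, and one degree of freedom; prognostic ones would offset part of this.

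The result rests on sound randomisation, a two-sided .05 level, 20 analysed per arm, and our count of tested variables. The damage is to the precision and interpretability of exploratory estimates that the Power Calculation section intends for planning larger trials. It does not reach type I error or the Aim 1 feasibility conclusions, so it is a free improvement to an exploratory pilot rather than a condition for going ahead.

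**What to change.** In Statistical Analyses, Aim 2, delete "any variables significantly different between groups at baseline" from the covariate sentence. Keep the outcome's baseline value and clinic location as the fixed covariates for every Aim 2 ANCOVA. If any further covariate is wanted, name it now, for each outcome it applies to, with the prognostic reason, so that nothing is left to choose later. Report baseline characteristics by arm with means and frequencies and drop the significance tests on them; the separate t test for adherence at 12 weeks is unaffected.

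The cost is about one sentence of wording and fewer tests to run. There is no change to sample size, data collection or the feasibility analysis. The number of covariates chosen by the data falls to zero.

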#### Pedometer Group

Participants will be provided with a digital pedometer (Digi-walker CW-700/701, YAMAX, San Antonio, TX). The pedometer records total number of steps (steps), activity time (hour/minute), distance walked (mile), and calories burned (kcal). The device stores this information every day and up to the previous 7 days. Weekly totals for steps, activity time, distance walked, and calories burned are stored for the current and previous week. The pedometer also displays a clock and an informative graph that estimates the number of calories burned based on the number of steps [51]. Participants will be instructed to log their daily steps, activity time, and distance walked measured by the pedometer in an activity diary.

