### Assessment Procedures

The primary purpose of this study is to investigate the feasibility and acceptability of a low-intensity intervention that combines 5 A’s counseling and an EAM system. We will also compare the effects of these high-tech activity monitors to low-tech ones (pedometers) on PA and other cardiovascular risk indicators (Framingham risk calculator, fitness). The study includes two assessments conducted at baseline and 12 weeks. Upon initial recruitment at the clinic, participants will provide informed consent and schedule their first assessment visit. Approximately 7 days before their initial assessment, participants will be given a baseline questionnaire and a research-grade activity monitor (discussed below) to wear for a 7 day baseline period. Participants will return to their primary care facility to complete the assessment. At 11 weeks, participants will be given a follow-up questionnaire and the research-grade monitor to wear for 7 days. At 12 weeks, participants will return to their clinic to complete assessments identical to baseline. As reimbursement for taking part in this study, all participants will receive a US $25 gift card at the end of the 12 week assessment, and at that time participants also forfeit their EAM or pedometer device.

The primary outcomes of interest are feasibility and acceptability. Feasibility will be operationalized in several ways. Number of days logged for activity, interactions with other users in the mobile app, and additional use of the app will be abstracted using procedures we have previously pilot tested successfully. Acceptability will be measured using self-report (modeled on items previously developed) [54], responses, and focus groups conducted after completion of the intervention. The primary physiological variables of interest include cardiovascular risk indicators and PA. Secondary outcome variables are anthropometrics, body composition, blood pressure, exercise motivation, health status and quality of life, physical function, psychological feelings, resting pulse, and self-regulation. All physiological study variables are listed in Table 4.

**Table 4 table4:** Study variables.

Variable		Measure	Subscales	Alpha statistics

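### Days worn is tested between arms as a single variable, but the two arms appear to record wear by different means

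*Protocol article*

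**What the plan says.** Under Statistical Analyses, Aim 1 sends the comparison of adherence between arms to Aim 2 and hypothesises that "the EAM group will show higher feasibility and acceptability compared to the pedometer group". Aim 2 then states: "Group mean values for adherence variables at 12 weeks (retention rate, days the monitor worn) will be analyzed by an independent" t test. The same Aim 2 text gives other rules for its baseline comparisons: "Differences in variable frequencies will be examined using chi-square tests", and "nonparametric tests (Kruskal-Wallis and Mann-Whitney U) for nonnormally distributed data". The general statement is "The alpha-level to determine significance is set at .05", with no sidedness given.

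The recording systems are described elsewhere:

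- **Pedometer.** The Pedometer Group section says "The device stores this information every day and up to the previous 7 days", with weekly totals for the current and previous week only. It also says: "Participants will be instructed to log their daily steps, activity time, and distance walked measured by the pedometer in an activity diary".
- **EAM.** The Introduction says EAMs sync wirelessly to an app. The Electronic Activity Monitors Group section says the app keeps all past activity and that a research account is added so activity can be viewed.
- **Feasibility measures.** Assessment Procedures says: "Number of days logged for activity, interactions with other users in the mobile app, and additional use of the app will be abstracted".

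The article does not define a worn day and does not name the source of days worn in either arm.

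**The concern.** For a between-arm test of days worn to be about wear, a worn day must be captured in the same way in both arms. In the EAM arm the device creates the record, subject to syncing. In the pedometer arm, the only record described that spans the intervention exists only if the participant writes it down. A blank diary day may mean the pedometer was not worn, or worn but not entered. A filled day may have been entered later from memory. The t test cannot separate recording behaviour from wear, and a larger sample would not remove the bias.

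At stake is one quantitative part of the claim that the EAM is the more feasible device. Under-recording in the diary would push the result towards that claim. If adherers are defined by days worn, which the article does not say, the adherers-only analysis would also select participants by different rules in the two arms.

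A second, smaller point is that retention is yes or no per participant, yet it is placed under the same t test.

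**Working it through.** The plan attaches no effect size, SD or power figure to the adherence test, so there is no stated figure to reproduce.

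**Inputs from the article.** There are 40 participants, with 5 of every 10 assigned to the EAM, so 20 per arm. Self-monitoring lasts 12 weeks, or 84 days. Alpha is 0.05, taken as two-sided.

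**Assumed inputs.** True wear is 70% of days in both arms, which borrows the Aim 1 benchmark value. The SD of days worn is 10 to 25 days. Between 5% and 20% of worn days are missing from the diary, and the EAM record is complete.

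**Step 1: false difference.**

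- True worn days: 0.70 × 84 = 58.8 in each arm.
- 5% undiarised: 58.8 × 0.05 = 2.9 days (3.5 percentage points).
- 10% undiarised: 58.8 × 0.10 = 5.9 days (7 points).
- 20% undiarised: 58.8 × 0.20 = 11.8 days (14 points).

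**Step 2: chance that the t test declares a difference when true wear is equal.** The standard error is SD × √(2/20). The noncentrality is the false difference divided by that standard error, and the critical value on 38 df is 2.024. For example, with SD 15 and 10% undiarised, the standard error is 15 × 0.316 = 4.74, the noncentrality is 5.88/4.74 = 1.24, and the rejection rate is 0.23.

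| SD (days) | 5% missing | 10% missing | 20% missing |
|---|---|---|---|
| 10 | 0.15 | 0.44 | 0.95 |
| 15 | 0.09 | 0.23 | 0.68 |
| 20 | 0.07 | 0.15 | 0.44 |
| 25 | 0.06 | 0.11 | 0.31 |

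The nominal rate is 0.05. Back-filling of days not worn would produce a false difference in favour of the pedometer.

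**Step 3: retention.** All possible tables with 20 per arm were enumerated.

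- The pooled t test and the uncorrected chi-square give the same decision in every table where the t test is defined.
- The t test's type I error is 0.050 at 80% true retention, 0.039 at 90% and 0.012 at 95%. Fisher's exact test has 0.023, 0.012 and 0.002.
- 20/20 against 16/20: t test p = 0.036, chi-square 0.035, Fisher 0.106.
- 19/20 against 14/20: t test p = 0.038, chi-square 0.037, Fisher 0.091. The Newcombe 95% CI for the difference is 0.008 to 0.473.
- If both arms retain everyone, the variance is zero and the t test is undefined. The chance of this is 0.90^40 = 1.5% at 90% true retention and 0.95^40 = 13% at 95%. The Newcombe interval still exists: for 20/20 against 20/20 it is −0.161 to 0.161.

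**The case against.** The strongest reply is that the article never says days worn comes from the diary in one arm and the app in the other. It says feasibility data are abstracted by procedures already piloted, and an article may leave such detail to the full protocol. This stands as a limit: the source contrast is inferred. The inference is strong, because a 7-day memory cannot cover 84 days and no other pedometer record is described. EAM capture also depends on syncing, so a missing EAM day is not certain non-wear either. That narrows the asymmetry without removing it.

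The analyses in Aim 2 are labelled exploratory, feasibility findings are mainly descriptive, and the article declines a yes/no feasibility verdict. Attrition, adverse events, technical difficulties, questionnaires and focus groups also bear on feasibility. All of this is fair and limits the consequence, but it does not make the wear contrast interpretable.

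Three stronger readings are tempting and are not supported:

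- A reader might infer that under-logging would make the pedometer arm fail the 70% wear benchmark. Aim 1 sets that benchmark for the intervention, not for each arm.
- A reader might infer that the t test on retention targets the wrong quantity or inflates error. The mean of 0/1 values is a proportion, so the mean difference is the risk difference, and the size is at or below nominal in the range checked (80% to 95% retention). The gap from Fisher's p-value reflects Fisher's conservatism.
- A reader might infer that Fisher's test is the necessary correction. In the 19/20 against 14/20 example it disagrees with the Newcombe interval, so naming both would leave the conclusion open.

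**Conclusion.** The concern holds for days worn. As described, the 84-day between-arm t test could show a difference that comes only from how wear was recorded. With equal true wear of 70% and 10% to 20% of worn days undiarised, the false difference is about 6 to 12 days and the false-positive rate about 0.11 to 0.95 across SDs of 25 down to 10 days. These figures rest on assumed wear, SD and diary completeness, and on the inference that the diary is the pedometer arm's 12-week record. The direction is not certain: non-recording favours the EAM and back-filling favours the pedometer.

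The retention point is minor. The named test departs from the chi-square rule that Aim 2 gives for frequencies, but it rarely affects the decision. The practical gain from changing it is a usable interval, including when retention is complete in both arms.

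**What to change.** 1. State the source of days worn in each arm and define a worn day in the same terms for both.
2. Do not treat the 84-day t test as evidence that one device is worn more. Report 84-day wear by arm descriptively, labelled with its source, with all randomised participants in the denominator.
3. Add a like-for-like comparison: read the pedometer's 7-day memory when the device is handed back at week 12, and set it against the EAM log for the same days. Count participants who do not return the device as not worn, or report them separately. This supports the 84-day figures and does not replace them.
4. Analyse retention as a difference in proportions with one interval chosen in advance, for example the Newcombe 95% CI.

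The cost is a short reading of a device that is already being collected, plus analysis wording. The downside is that the comparable window is a single atypical week, just before a scheduled visit and while the research-grade monitor is also worn, and early dropouts contribute only through the non-return rule.
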